### Sample size calculations

The primary endpoint of this study is oxygenation index measured at T4. According to literature [16], oxygenation index for patients inhaling pure oxygen and under well oxygenated conditions during TLV usually ranges between 350-400 mmHg and drops to 150-200 mmHg after patients are switched to OLV. Therefore, during OLV, changes in oxygenation index within the limit of 50 mmHg would be clinically insignificant. Thus, the cut-off value for inferiority is set to 50 mmHg. In other words, in our study, if oxygenation index measured at T4 of the study group is below that of the control group, but the difference between that of the two groups is within 50, then the ventilation strategy of the study group is not inferior to that of the control group in terms of improving intraoperative oxygenation. We set probability of type 1 error at α = 0.025, probability of type 2 error at β = 0.20, and power value at 0.80; a sample size of 38 is calculated for each group by using PASS 11.0 software. Considering a 10% removal and dropout rate, a final sample size of 42 is required for each group.

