### Statistical analysis

The research team will cooperate with medical statisticians to analyze data after completing the trial. SPSS 20.0 software will be applied for data processing. Dropout or lost to follow up cases will be reported. Per-protocol analyses will be applied for all data. Under circumstances of missing values, multiple imputation shall be conducted. Kolmogorov–Smirnov analysis will be performed to discern normally distributed data. Normally distributed data will be presented as mean $$\pm$$ standard deviation (SD), while discrete data will be presented as median and interquartile range. Independent-samples T test will be adopted for univariate analysis of normally distributed data. Pearson correlation test will be used to test the linear relationship between two variables. Mann–Whitney U test will be applied for discrete data. Categorical variables will be expressed as relative risk ratio and assessed by Fisher’s exact test or chi-square tests, if applicable. 95% CI will be employed to express confidence level of all parameters. *P* value < 0.05 shall be defined as statistically significant.

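### The only non-inferiority rule in the protocol compares the measured T4 difference with 50 mmHg and ignores its standard error, so it does not deliver the stated α of 0.025

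*Protocol article*

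**What the plan says.** The Background section frames the hypothesis as non-inferiority. The Sample size calculations section fixes the endpoint ("The primary endpoint of this study is oxygenation index measured at T4") and the margin ("Thus, the cut-off value for inferiority is set to 50 mmHg"). It then restates the margin as an if/then rule: where the index measured at T4 is lower in the study group, "but the difference between that of the two groups is within 50, then the ventilation strategy of the study group is not inferior". The same section sets the error rates, "We set probability of type 1 error at α = 0.025" and "probability of type 2 error at β = 0.20, and power value at 0.80", and reports that "a sample size of 38 is calculated for each group by using PASS 11.0 software".

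The Statistical analysis section is general. It says "Independent-samples T test will be adopted for univariate analysis of normally distributed data" and that a P "value < 0.05 shall be defined as statistically significant". It also plans 95% confidence intervals for all parameters. Neither section links a confidence limit, or a test shifted by the margin, to the 50 mmHg cut-off.

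**The concern.** A non-inferiority claim with a one-sided error of 0.025 requires the data to exclude a deficit as large as the margin, which means that a confidence limit must clear -50 mmHg. The written rule asks only that the difference between the measured group values be smaller than 50. It contains no standard error, so the result does not have to be precise and the stated α does not describe it.

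The analysis section does not fill the gap. An ordinary two-sample t test at P < 0.05 addresses a difference of zero, not a deficit of 50 mmHg. The confidence intervals that could carry the decision are planned, but they are given no role in it. At stake is the error rate of the trial's main conclusion: an analyst who follows the text literally would apply a rule far more lenient than the one implied by α = 0.025 and 38 per group.

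**Working it through.** **Inputs from the Sample size calculations section.** Margin 50 mmHg; α = 0.025, sidedness not stated and read here as one-sided, the usual convention for non-inferiority; power 0.80; 38 per group before dropout.

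**Not given.** The SD and the assumed true difference. I take the true difference used for planning as 0, solve for the SD, and show a range of 50 to 100 mmHg.

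**1. The plan's own figure.** For a confidence-limit rule, n per group = 2 × SD² × (z₀.₉₇₅ + z₀.₈₀)² / 50².
- With SD = 77: 2 × 5929 × (1.960 + 0.842)² / 2500 ≈ 37.2, rounded up to 38.
- SDs that round to 38 run from about 76.8 to 77.7 with this formula, and from 75.8 to 76.7 with the t-based version.

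So 38 fits a standard confidence-limit design if the SD is about 77. It cannot be reproduced independently, because the SD is not stated.

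**2. Standard error.** SE = SD × √(2/38). This gives 11.47 for SD 50, 17.67 for SD 77 and 22.94 for SD 100.

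**3. Written rule at the margin.** Let δ be the true difference, study minus control. Then P(measured difference > -50) = Φ((δ + 50)/SE). At δ = -50 this is Φ(0) = 0.50, whatever the SD or n, provided the estimate is unbiased and roughly symmetric. In 200,000 simulated trials (SD 77, 38 per group) the rate was 50.1%. If only measured differences between -50 and 0 count, as the sentence literally says, the rate is 48.5% to 50.0% for SDs of 50 to 100.

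**4. Beyond the margin, and the confidence-limit rule beside it (38 per group).**

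| SD (assumed) | True loss 60: written rule | True loss 60: CI rule | True loss 70: written rule | True loss 70: CI rule |
|---|---|---|---|---|
| 50 | 19.2% | 0.2% | 4.1% | 0.01% |
| 77 | 28.6% | 0.6% | 12.9% | 0.1% |
| 100 | 33.2% | 0.8% | 19.2% | 0.2% |

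For example, at SD 77 and a true loss of 60: Φ((-60 + 50)/17.67) = Φ(-0.566) = 0.286.

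**5. What the confidence-limit rule requires.** At SD 77 the 95% half-width is 1.99 × 17.67 ≈ 35.2, so the measured deficit may be at most 50 - 35.2 = 14.8 mmHg. A measured deficit of 49 would pass the written rule, although its interval runs from about -84 to -14 and so reaches well past the margin. At a true loss of exactly 50 the confidence-limit rule passes 2.5% of the time (simulated 2.48%). At a true difference of 0 its power is 79.8%, which matches the stated 0.80.

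**The case against.** The strongest defence is that the sentence is a plain-language gloss on the margin. It sits in the sample size section, directly after the cut-off, and does not use the word observed. The margin, the α of 0.025 and the 38 per group all fit a confidence-limit design, and a two-sided 95% interval is the one that matches that α. The ingredients of the correct rule are therefore present, and the authors may well have meant it. The analysis paragraph is also generic, and a separate analysis plan may exist.

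Much of this stands as an account of intent, but it does not repair the text. The sentence is an if/then verdict on the index as measured at T4, it is the only criterion in the document, and nothing joins the planned intervals to -50. The point concerns a rule that is stated wrongly, not detail left to an analysis plan. A later plan with a confidence-limit rule would conflict with the protocol as it reads.

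Two stronger readings are tempting and should not be drawn:
- A reader might infer that the rule is shown to be wrong because one dataset could be both significantly worse and not inferior. A correct rule allows that too. With SD 50 and 38 per group, a measured -25 has a 95% interval of -25 ± 22.9, or -47.9 to -2.1: below zero, yet clear of the margin.
- A reader might infer that the same interval would support a superiority claim if it lay above zero. The Background states only a non-inferiority hypothesis, and all analyses are per protocol, so the documents plan no such claim.

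**Conclusion.** The point holds. Followed as written, the criterion has a false non-inferiority rate of about 50% at a true 50 mmHg deficit, twenty times the stated 2.5%. That figure does not depend on the missing SD or on n, but it does need an unbiased, roughly symmetric estimate. The per-protocol exclusion of deviating patients, including those given rescue manoeuvres, could disturb that condition. The 28.6% pass rate for a true loss of 60 mmHg rests on an assumed SD of 77 and a one-sided reading of α; across SDs of 50 to 100 it is 19% to 33%.

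The documents do not show that the investigators intend to disregard uncertainty, since 95% intervals are planned. What they show is that the only stated decision rule does not use them. Because the rule governs the primary conclusion, it should be corrected before the analysis.

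**What to change.** In Sample size calculations, replace the if/then sentence, and repeat the new text in Statistical analysis, along these lines: non-inferiority is concluded only if the lower limit of the two-sided 95% confidence interval (one-sided α = 0.025) for the mean difference in T4 oxygenation index, study minus control, lies above -50 mmHg. Add that the P < 0.05 test of zero difference plays no part in that claim.

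This costs two sentences and needs no additional patients or data. The claim becomes harder to reach than under the present wording. If the unstated planning SD was about 77 mmHg, power stays at the intended 80% with 38 evaluable per group. If the true SD is 100, power at zero difference falls to about 58%.

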**Methods:**

A total of 84 patients scheduled for elective pulmonary lobe resection necessitating one lung ventilation will be recruited and randomized totwo parallel groups. For all patients, one lung ventilation is initiated the right after patients are turned into lateral decubitus position. For patients in the study group, individualized PEEP titration is started the moment one lung ventilation is started, while patients in the control group will receive a recruitment maneuver followed by individualized PEEP titration after initiation of one lung ventilation. The primary endpoint will be oxygenation index measured at T4. Secondary endpoints will include intrapulmonary shunt, respiratory mechanics, PPCs, and hemodynamic indicators.

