## Methods/design

### Objectives and design

This parallel, two-arm, single-center, prospective, single blind (investigator-initiated, assessor-blinded), randomized, controlled trial tests the hypothesis that applying sufficient PEEP without RM right after patients are turned into lateral decubitus position is an effective strategy for patients receiving one lung ventilation. 84 patients will be randomly divided into one of two different groups (see Consolidated Standards of Reporting Trials [CONSORT] diagram, Fig. 1). The SPIRIT 2013 Checklist is given in Additional file 1.

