### Blinding, data collection, randomization and record keeping

This is a single-blind randomized clinical trial. Demographic data, results of laboratory tests, history of previous illnesses, fluid balance, hemodynamic variables, anesthesia-associated variables, respiratory parameters and postoperative clinical status will be collected and recorded onto case report forms (CRF). All patients meeting the inclusion criteria will be randomly allocated to the study group and the control group in a ratio of 1:1. Randomization will be carried out by means of a computer-generated blocked randomization form, with 17 blocks of five patients per block. Allocation will proceed with opaque, sealed and numbered envelopes. Subjects will be recruited and assigned in numeric order. All original records (CRF and associated correspondence) will be archived and safeguarded for 10 years and then destroyed, as required by hospital standards.

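### Blocks of five cannot deliver the stated 1:1 allocation, and the 85-slot list does not secure 42 patients per group

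*Protocol article*

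**What the plan says.** The randomization section (Blinding, data collection, randomization and record keeping) says that eligible patients will be "randomly allocated to the study group and the control group in a ratio of 1:1". The next sentence describes a computer-generated blocked list "with 17 blocks of five patients per block", to be applied through numbered, sealed envelopes in numerical order.

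The total is consistent elsewhere. The abstract has "A total of 84 patients scheduled for elective pulmonary lobe resection necessitating one lung ventilation will be recruited" and the design section has "84 patients will be randomly divided into one of two different groups". The sample size section builds up to the same total: "a sample size of 38 is calculated for each group by using PASS 11.0 software", followed by "Considering a 10% removal and dropout rate, a final sample size of 42 is required for each group". Its error settings are "We set probability of type 1 error at α = 0.025" and "probability of type 2 error at β = 0.20, and power value at 0.80".

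**The concern.** Blocking is used so that the arms are equal in size each time a block is completed. That needs a block size divisible by the sum of the ratio terms, which for 1:1 is two. Five is not. The article therefore fixes a ratio and a block size that cannot both hold.

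Two things follow. First, every completed block is out of balance by one patient, in a direction the article does not specify, and these imbalances can accumulate over 17 blocks. Second, the list length does not match the planned total, and an odd number of places cannot be shared equally. The sample size section relies on 42 in each arm, and the list as described does not secure that number. A reader also cannot reconstruct the allocation procedure, because 3:2 in every block, alternating 3:2 and 2:3, and a random choice between them would all fit the words and give different arm sizes.

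**Working it through.** **Inputs.** Block size 5, 17 blocks and ratio 1:1 (randomization section). 42 per group, 38 evaluable per group, 10% loss, margin 50 mmHg, α = 0.025 and power 0.80 (sample size section). Total 84 (abstract and design section).

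**1. The plan's own totals.** 2 × 42 = 84, which agrees in all three places. The list has 17 × 5 = 85 places. Since 84/5 = 16.8, 17 is the fewest whole blocks of five that cover 84.

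**2. Balance.** 5/2 = 2.5 and 85/2 = 42.5. Neither is a whole number, so neither a block nor the full list can be split equally. The closest possible split of a filled list is 43 and 42.

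**3. How far the arms could drift.** Assumption: each block is 3:2 or 2:3 with equal chance. Let X be the number of blocks that favour the study group, X ~ Binomial(17, ½). The study group then has 2 × 17 + X = 34 + X patients.
- The split is 42 and 43 only if X = 8 or 9: 2 × C(17,8)/2^17 = 2 × 24,310/131,072 = 0.371.
- Smaller arm at 41 or fewer: 1 − 0.371 = 0.629, about 63%.
- Smaller arm at 40 or fewer: 1 − 2 × (24,310 + 19,448)/131,072 = 0.332, about 33%.
- If every block leans the same way, the arms are 51 and 34.

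**4. If recruitment stops at 84 and the last envelope is unused.** Under the same assumption, the first 16 blocks give the study group 32 + Y, Y ~ Binomial(16, ½). The four used places of the last block give it 2 with probability 0.6, and 1 or 3 with probability 0.2 each. Then P(42 and 42) = 0.6 × C(16,8)/2^16 + 0.4 × C(16,7)/2^16 = 0.6 × 12,870/65,536 + 0.4 × 11,440/65,536 = 0.188. Exact equality is possible but occurs in only about 19% of such lists.

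**5. What this does to power.** The article gives no SD. Reading α as one-sided, the SD implied by 38 per group under the normal approximation is 50 × √(38/2)/(1.960 + 0.842) = 77.8 mmHg (an assumption). For unequal arms the equivalent equal arm size is 2ab/(a + b).
- Arms of 40 and 45: 2 × 40 × 45/85 = 42.4, or 38.1 after 10% loss; power 0.801.
- Extreme arms of 34 and 51: 2 × 34 × 51/85 = 40.8, or 36.7 after 10% loss; power 0.786.

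**6. Companion check on the loss allowance.** 38/(1 − 0.10) = 42.2, which is 42 to the nearest whole number and 43 if rounded up. 38 × 1.10 = 41.8 also rounds to 42. Conversely, 42 × 0.90 = 37.8. In whole patients, losing 4 of 42 (4/42 = 9.5%) leaves 38, and losing 8 of 84 leaves 76 = 2 × 38. At 37.8 per group and the implied SD, power is 0.798.

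**The case against.** **The list is only one place too long.** The abstract, the design section and the sample size section all give 84, and nothing names 85 as a target. Seventeen is what one gets by completing the last block of five. This stands. A reader might infer that the protocol carries a third, competing sample size, but it does not: 85 is a list length. The mismatch is a by-product of the block size.

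**The loss inflation is wrong and the trial is too small.** A reader might infer this from 42 × 0.90 falling below 38. The documents do not support it. The gap is 0.2 of a patient per group, 42.2 rounds to 42, and the article gives no formula from which a mistaken method could be established. Power at exactly 10% loss is about 79.8%, under an SD that has to be back-calculated.

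**Imbalance hardly matters.** Largely true for power, as step 5 shows. It does not remove the contradiction, because the article promises 1:1 and 42 per group and describes a list that guarantees neither.

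**An article condenses the full protocol.** A rule for the composition of blocks could be set out there. That could explain how the fives are divided, but no rule makes five divisible by two, and the article itself fixes both the ratio and the block size.

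**Conclusion.** The point holds as a minor inconsistency in the randomization section. A 1:1 ratio and blocks of five are incompatible; this is certain and needs no assumption. A filled list of 85 cannot give equal arms. The chance of about 63% that the smaller arm falls below 42 depends on the assumption that blocks are 3:2 or 2:3 at random; a strictly alternating rule would give 43 and 42, and a constant one 51 and 34.

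The consequence is loss of guaranteed balance and an allocation procedure that cannot be reproduced from the text. Nothing here shows biased allocation, a material loss of power or a need for more patients. The loss allowance is a rounding matter only.

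**What to change.** In the randomization section, replace the blocks of five with even block sizes that total 84: for example 21 blocks of 4, 14 blocks of 6, or a mix such as 9 blocks of 4 and 8 blocks of 6 (36 + 48 = 84). Each gives exactly 42 per group when the list is filled. If the list in use already has even blocks, only the sentence needs correcting. If it really is in fives, state how each block is divided and how the unused part will be handled.

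Optionally, add to the sample size section that 42 per group leaves 38 if no more than 4 per group (9.5%) are lost.

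The cost is one corrected sentence, one optional sentence and, at most, a regenerated list for patients not yet randomized. The planned total stays at 84.

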### Statistical analysis

The research team will cooperate with medical statisticians to analyze data after completing the trial. SPSS 20.0 software will be applied for data processing. Dropout or lost to follow up cases will be reported. Per-protocol analyses will be applied for all data. Under circumstances of missing values, multiple imputation shall be conducted. Kolmogorov–Smirnov analysis will be performed to discern normally distributed data. Normally distributed data will be presented as mean $$\pm$$ standard deviation (SD), while discrete data will be presented as median and interquartile range. Independent-samples T test will be adopted for univariate analysis of normally distributed data. Pearson correlation test will be used to test the linear relationship between two variables. Mann–Whitney U test will be applied for discrete data. Categorical variables will be expressed as relative risk ratio and assessed by Fisher’s exact test or chi-square tests, if applicable. 95% CI will be employed to express confidence level of all parameters. *P* value < 0.05 shall be defined as statistically significant.

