#### Subgroup analysis

Patients will be divided into subgroups according to the side of surgery. Subgroup analysis will be conducted to further explore the effect of our trial intervention on intraoperative oxygenation. Post-hoc analysis will be applied for subgroup analysis.

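### The only test stated for the T4 oxygenation index is an unadjusted t test, which is valid but probably gives away precision that baseline data already collected could supply

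*Protocol article*

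**What the plan says.** In the protocol article, Sample size calculations fixes the endpoint and the decision rule: "The primary endpoint of this study is oxygenation index measured at T4" and "Thus, the cut-off value for inferiority is set to 50 mmHg". The design values are "We set probability of type 1 error at α = 0.025" and "probability of type 2 error at β = 0.20, and power value at 0.80", from which "a sample size of 38 is calculated for each group by using PASS 11.0 software". No SD is given.

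Statistical analysis sets one rule per data type. For normally distributed data it is "Independent-samples T test will be adopted for univariate analysis of normally distributed data". No separate method is given for T4, and no regression or ANCOVA is named.

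The relevant covariates are already in the plan:

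- Study endpoints lists oxygenation index at T0 (before induction), T1 (after intubation) and T2 (after tube adjustment in the lateral position).
- Mechanical ventilation starts group-specific ventilation only after tube position has been confirmed in the lateral position.
- Study visits and data collection includes side of surgery.

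The randomization section describes blocking and no stratification. Side is used only under Subgroup analysis: "Patients will be divided into subgroups according to the side of surgery", followed by "Post-hoc analysis will be applied for subgroup analysis".

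**The concern.** The conclusion depends on where a confidence limit falls relative to a 50 mmHg margin, so interval width matters directly, and planned power is only 0.80. If a patient's oxygenation before the groups diverge, or the side operated on, predicts oxygenation at T4, an unadjusted comparison counts that explainable variation as noise. Nothing further need be measured to use either variable. Side is also a proper pre-treatment covariate: the exclusion for a bulla on the dependent lung means it must be known at screening.

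The subgroup wording raises a smaller matter. A subgroup named in the protocol before outcome data exist is not post hoc, and that label undersells a planned analysis. The section also names no comparison of the treatment effect between sides.

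**Working it through.** **Inputs from the article (Sample size calculations):** margin 50 mmHg; α = 0.025; power 0.80; 38 evaluable per group.

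**Assumptions:** α read as one-sided, in line with the non-inferiority aim; true difference 0; SD back-solved; joint correlation ρ of the covariates with T4 varied from 0 to 0.7.

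**Step 1: the article's 38 per group.** Without an SD the figure cannot be reproduced independently, only solved backwards. From n = 2(1.960 + 0.842)² SD² / 50², setting n = 38 gives SD = 50 / (2.802 × √(2/38)) = 77.8 as the upper limit. After rounding up to whole patients, SDs of 76.8 to 77.7 give 38 (normal approximation); on the t distribution the range is 75.8 to 76.7. SD 76.8 is used below. Reading α as two-sided 0.025 would imply an SD of about 70.7.

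**Step 2: unadjusted t test, 38 per group.** SE = 76.8 × √(2/38) = 17.62. Half-width = 1.9925 × 17.62 = 35.1 mmHg (74 df). Noncentral-t power = 0.800.

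**Step 3: ANCOVA with two covariates.** Residual SD = 76.8 × √(1 − ρ²). Two degrees of freedom are charged (72 df), and the SE is inflated for chance covariate imbalance by √(1 + 2/71) = 1.014. Half-width = 1.9935 × 17.62 × 1.014 × √(1 − ρ²).

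| Joint ρ | Residual SD | Power | Half-width (mmHg) |
|---|---|---|---|
| t test | 76.8 | 0.800 | 35.1 |
| 0 | 76.8 | 0.788 | 35.6 |
| 0.1 | 76.4 | 0.792 | 35.4 |
| 0.2 | 75.2 | 0.805 | 34.9 |
| 0.3 | 73.3 | 0.825 | 34.0 |
| 0.5 | 66.5 | 0.890 | 30.8 |
| 0.7 | 54.8 | 0.972 | 25.4 |

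Break-even lies between ρ = 0.1 and 0.2. The proportional change in half-width does not depend on the SD.

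**Step 4: side alone.** With an assumed 60/40 split and one covariate charged, a mean T4 difference between sides of 0, 20, 40 or 60 mmHg gives R² of 0, 0.016, 0.065 or 0.146 and power of 0.794, 0.801, 0.820 or 0.853. Side by itself helps only if the sides differ substantially.

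**Step 5: treatment-by-side interaction.** Assuming an even left/right split there are 19 patients per arm per side. The unadjusted SE of the interaction is 77 × √(4/19) = 35.3 mmHg, so the 95% half-width is 1.99 × 35.3 ≈ 70 mmHg, wider than the margin.

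**The case against.** The strongest reply is that nothing here is an error. An unadjusted t test after 1:1 randomization is a valid analysis and fits an unadjusted sample size. The quoted sentence is a general rule that neither names T4 nor rules out an adjusted model, and a separate analysis plan, not available here, could specify one. All of that stands, so the point is about efficiency. The rule reaches T4 only because the article gives no other method.

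The size of the gain also rests on assumed inputs. T1 is taken supine after intubation, at an FiO2 the text does not state, whereas T4 is taken during lateral one-lung ventilation on pure oxygen with the other lung collapsed. The article itself describes a fall from 350–400 to 150–200 mmHg between two-lung and one-lung ventilation. Nothing in it supports a strong T1–T4 correlation. This stands too, and is why ρ = 0 is in the table. T2, in the lateral position, may predict T4 better.

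A reader might infer more than the article supports:

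- **That adjustment is free.** It is not quite: two uninformative covariates cost about one point of power.
- **That unstratified allocation leaves the t test biased by chance imbalance.** The t-based interval already allows for random imbalance; adjustment reduces its contribution and does not correct an invalid result.
- **That separate left and right tests are planned.** The subgroup text says only that patients will be divided to explore the effect further. It does not say how the sides will be compared.
- **That an interaction would settle whether the effect differs by side.** With a half-width near 70 mmHg it would not.

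**Conclusion.** The point holds as probable lost precision, with no fault of validity. The article names only an unadjusted test for a normally distributed T4, while pre-divergence oxygenation index and side of surgery will be on file for use. Measured against the unadjusted 0.80 and 35 mmHg, the effect of adjusting runs from about 1 point of power lost and half a millimetre of mercury added to the half-width (ρ = 0), to about 17 points gained and nearly 10 mmHg removed (ρ = 0.7). A gain needs a joint ρ above roughly 0.1 to 0.2. These figures rest on the back-solved SD, a one-sided α, a zero true difference and assumed correlations. The balance favours adjusting because the possible loss is small and bounded. The subgroup label is a secondary wording matter.

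**What to change.** Before outcomes are examined by arm:

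1. Specify the primary estimate as the adjusted mean difference (study minus control) in T4 oxygenation index from ANCOVA with treatment, one named pre-divergence oxygenation index and side of surgery. The baseline should be T1, or T2 provided that it is sampled before group-specific ventilation begins. It must not be T3, which is measured after the groups diverge.
2. Compare the lower bound of the two-sided 95% CI with −50 mmHg.
3. Keep the unadjusted t-based CI as a sensitivity analysis.
4. Drop the post-hoc label for the side subgroup. Report the treatment-by-side interaction with its CI in a separate exploratory model and state its low precision. Putting the interaction in the primary model could turn the treatment coefficient into the effect on one side only, which is not the quantity to set against the margin.

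The cost is a change of wording: no new measurements or patients are needed, and two degrees of freedom are used. If a separate analysis plan already adjusts, the published text needs only to be aligned with it.
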